## Ethical considerations

*Consequences and advantages of the study*

The study will not directly implicate changes in the treatment of CKD for the individual patient. For the group of patients who suffer from CKD the study aims to reveal possible effects of treatment with eplerenone on arterial stiffness. The result of this could lead to improvement of the prognosis for the CKD patient and the risk of CV disease and death as well as attenuation of progression of uraemia.

*Draw backs and risks of the study*

1: use of time

2: discomfort of having blood samples drawn

3: inconvenience when collecting urine

4: inconvenience when having AMBP device mounted

5: side effects of study medication, including the risk of hyperkalaemia

Re 1: The time used for the patient is quite a lot, but the many visits secure that it is a safe intervention. This is to insure a detection of hyperkalaemia in good time. The many visits also induce a better compliance.

Re 2: At the times of blood sampling a maximum of 68 ml will be drawn. This is done on the first and last visits only. In the remainder of visits, a max. of 54 ml is drawn. This constitutes no risk for the patient.

Re 3: It can be inconvenient to collect urine more often than in a usual outpatient course.

Re 4: Some patients think it tiresome to wear the AMBP device for 24 hours. It is used as a routine examination modality in daily clinical practice. Rarely there are marks from the cuff in the days after the measurements. There are no risks in connection with this examination.

Re 5: Common side effects from the active study drug are seen in more than 1 % and less than 10 % of patients. These can be nausea, diarrhoea, dizziness, hypotension, reduced kidney function and hyperkalaemia. Reduction in kidney function is reversible. The risk of hyperkalaemia is met by the close monitoring plan as described above. The investigational group has good clinical experience in the use of eplerenone in this type of patients.

According to the SPC the following uncommon side effects have been reported in more than 1‰ and less than 1% of patients:

Pyelonephritis, eosinophilia, dehydration, hypercholesterolemia, hypertriglyceridemia, hyponatremia, insomnia, headache, orthostatic hypotension, arterial thrombosis in the leg, atrial fibrillation, myocardial infarction, left ventricular dysfunction, respiratory disorders, disorders in the thorax and mediastinum, pharyngitis, flatulence, vomiting, pruritus, increased perspiration, back ache, leg cramps, asthenia, discomfort, increase in blood urea nitrogen, increased plasma creatinine.

## Adverse events and side effects

Registration and reporting of side effects follow the given laws. In the following the document of referral is in Danish: *Bekendtgørelsen for kliniske forsøg med lægemidler på mennesker* (The notice for clinical studies using pharmaceutical drugs on humans). Suspected and unexpected adverse reactions (SUSAR), that are either lethal or life threatening will be reported to the Danish Medicines Agency within 7 days of notice to the sponsor-investigator and at the latest at day 8 after this the Agency will be informed of all actions taken on the follow up. All unexpected and serious suspected side effects will be reported to the Danish Medicines Agency at the latest 15 days after it has come to the attention of the sponsor-investigator. Serious adverse reactions (SAR) will be reported on a yearly basis to the Regional Ethics Committee. Events will be recorded on the patients’ CRF excepting laboratory results that lie outside the reference values but where no action is taken to either change the study medication or institute treatment. Common viral diseases such as colds or flus will not be reported. Finally uncomplicated urinary tract infections will not be reported.

Events and side effects will be reported in the final report to the Danish Medicines Agency after termination of the study. Events and side effects will be registered from the time of initial dosing of study medication until withdrawal.

In case of unacceptable side effects the participant will be withdrawn from the study. The patient will continue in the out patients clinic of nephrology as long as this is required.

The study can be terminated before time according to the sponsor-investigator’s judgement.

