### 3.2 Design

The study is a prospective, randomized, controlled, parallel group, phase IV study.

| Week number | -4 | 1 | 2 | 4 | 8 | 12 | 16 | 20 | 24 |
| --- | --- | --- | --- | --- | --- | --- | --- | --- | --- |
| Visit number |  | 1a/1b | 2 | 3 | 4 | 5a/5b | 6 | 7 | 8a/8b |

A BP target of 120-130/80-90 is set and investigators will strive to keep this constant in patients throughout their enrolled period. Therefore a run-in period of 4 weeks has been planned. All patients are to continue on their normal medication including blockers of RAS, which most of these patients receive before enrolment. If anti-hypertensive treatment needs to be intensified, this is done by adding beta blocker, calcium antagonist or methyldopa. If BP is lower than target pressure medication will be withdrawn, primarily via reduction in calcium antagonism or beta blockade, while RAS-blockade in the initial form is aimed to be kept as it was.

If study participants fail to tolerate the full dose of eplerenone 50 mg once daily, dose will be reduced to 25 mg once daily. In case of the patients receiving potassium supplements at time of enrolment these will be withdrawn before start of intervention.

Participants are randomized after the run-in period and are given consecutive numbers of identification.

The study plan is identical for the two groups.

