### 3.3 Endpoints

Primary endpoint is the difference in PWV measured by the tonometer (Millar, Houston, Texas, USA) and using the SphygmoCor® hard- and software.

Secondary endpoints are pulse wave morphology, evaluated by the AIx, BP, subendocardial viability ration (SEVR), heart rate, time to reflection (TR), ejection duration (ED), pulse pressure (PP), kidney function (estimated glomerular filtration rate (eGFR)), p-creatinine, AASI and albuminuria.

P-potassium and p-creatinine are used for safety monitoring.

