AMBPs are automatically measured blood pressures during ordinary daily activities for a time period of approximately 24 hours. AMBP has been found reproducible in population studies (25-30), hypertensive populations (46) and diabetics (47). The reproducibility of AASI has been proven less reliable in an essentially hypertensive population (48) . The brachial BP is measured in the office using the ABPM equipment on the non-dominant arm. After manual measurements the apparatus will automatically measure the BP every 15 minutes in daytime, which is defined from 7 am until 11 pm. Hereafter the measurements will be performed every 30 minutes from 11 pm till 7 am (49). All patients receive a diary in which they are to make notes of physical activity, meals and rest as well as bedtime and rising time in the morning. For calculation of AASI a minimum of 21 readings of BP is required. These must be spread out over the whole period with at least 7 successful readings during night time. AASI is calculated in the following manner: (1-(the slope of diastolic BP/slope of systolic BP)). It follows that the stiffer the arterial tree, the more the regression line will go towards 0 and AASI thus towards 1. Previous studies have provided references for AASI in the background population. AASI for normotensive individuals is 0.57. In younger individuals AASI is 0.53 increasing to 0.72 in the elderly (30).

*Intervention – study medication*

The study medication is eplerenone, a selective aldosterone receptor antagonist. It is an approved drug, which in this study will be used on a non-appraised indication. The Summaries of Product Characteristics (SPC) in Danish will be used as reference document for evaluation of possible side effects and will be accessible at the site of investigation when the study is initiated.

Initial recommended dose is 25 mg once daily. The dose will be increased to 50 mg eplerenone in once daily dosing after 1 week. In this study eplerenone will be added to the study participants’ usual medication. The manufacturing company Pfizer Aps has been informed of the study.

*Control*

The control group will continue their usual medical therapy.

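### An out-of-range potassium or creatinine counts as an event only if someone acts on it, and one of the two qualifying actions cannot occur in controls, so laboratory event counts are not ascertained alike in the two arms

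*Protocol*

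**What the plan says.** The section on adverse events and side effects sends events to the CRF, "excepting laboratory results that lie outside the reference values but where no action is taken to either change the study medication or institute treatment". Events and side effects then go to the medicines agency in the final report.

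Section 3.4 defines the two arms. On the active side, "The study medication is eplerenone, a selective aldosterone receptor antagonist". On the other, "The control group will continue their usual medical therapy". No placebo or blinding is described. Section 3.2 gives one foreseen change of study medication: "If study participants fail to tolerate the full dose of eplerenone 50 mg once daily, dose will be reduced to 25 mg once daily".

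Section 3.3 states: "P-potassium and p-creatinine are used for safety monitoring". P-creatinine and eGFR are also secondary endpoints there; potassium is not. Under Ethical considerations the common side effects are listed ("These can be nausea, diarrhoea, dizziness, hypotension, reduced kidney function and hyperkalaemia"), the many visits are justified by timely detection of hyperkalaemia, and "The risk of hyperkalaemia is met by the close monitoring plan as described above".

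Section 3.10 has laboratory results entered into a database. Sections 3.11 and 3.13 schedule the same blood tests and visits for both groups.

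**The concern.** Whether an abnormal laboratory value becomes an event depends on what the investigator does, not on the value. Changing study medication is possible in one arm only, and with no placebo whoever decides on the action can know the allocation.

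Take two patients with the same raised potassium. If the eplerenone dose is reduced, the first has an event. If the second, a control, is only re-tested, there is none. Reducing one of a control's usual drugs because of the value is not a change of study medication, and it is not clearly the start of a treatment either. An eplerenone patient whose high value is tolerated also produces no event.

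At stake is how the final report is read on hyperkalaemia, the risk for which the visit schedule was designed, and on creatinine rises. A difference between arms in laboratory events would mix the drug's effect with differences in how values were handled.

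**Working it through.** The protocol gives no rate of abnormal values and no action rate, so it has no figure of its own to reproduce on this point. Its one computed figure, the sample size for PWV, does not bear on it.

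**Step 1: routes to an event, from the text.**

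| | Eplerenone | Control |
|---|---|---|
| Study medication changed | possible (dose reduction, 3.2) | not possible (usual therapy only, 3.4) |
| Treatment instituted | possible | possible |
| No action | no event | no event |

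**Step 2: recording probability, on assumptions.** Given an abnormal value, let t be the probability that treatment is instituted, equal in both arms. Let d be the probability that study medication is changed, on eplerenone only and independent of t.

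- Control: P(recorded) = t
- Eplerenone: P(recorded) = 1 − (1 − t)(1 − d)

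The second exceeds the first whenever d > 0 and t < 1.

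**Step 3: illustrative numbers.** Abnormal values are assumed equally frequent in both arms, so the true ratio is 1. Ratio of recorded events, eplerenone to control:

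| t | d = 0 | d = 0.2 | d = 0.5 | d = 0.8 |
|---|---|---|---|---|
| 0.1 | 1.00 | 2.80 | 5.50 | 8.20 |
| 0.3 | 1.00 | 1.47 | 2.17 | 2.87 |
| 0.5 | 1.00 | 1.20 | 1.50 | 1.80 |

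Example: if 20% of the planned 40 per arm have an abnormal value (8 patients each), with t = 0.3 and d = 0.5:

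- Control: 8 × 0.3 = 2.4 recorded, 5.6 not.
- Eplerenone: 8 × (1 − 0.7 × 0.5) = 8 × 0.65 = 5.2 recorded, 2.8 not.
- Ratio: 5.2 / 2.4 = 2.17.

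**Step 4: relaxing equal t and independence.** In general, at equal frequency of abnormal values, the ratio is the probability of any qualifying action on eplerenone divided by that in controls. If a dose change on eplerenone merely replaces the treatment that a control would receive, the two probabilities can be equal, for example 0.3 / 0.3 = 1.00. It falls below 1 if controls are acted on more often.

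**Step 5: what the rule leaves untouched.** The exemption governs event entries. Potassium and creatinine are measured at baseline and at seven later blood-sampling visits (weeks 2, 4, 8, 12, 16, 20 and 24) in both groups, and the results enter the database. The Statistics section applies t tests to the secondary endpoints, which include creatinine and eGFR. It describes no comparison of potassium.

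**The case against.** The strongest reply is that nothing is lost. Every value is drawn on the same schedule and kept, and kidney function is compared by value whatever action followed. This stands. A reader might infer that tolerated high values go unrecorded, or that the comparison of kidney function is biased. The protocol supports neither: only the event label is missing.

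It can also be said that no test of event counts is planned, and that threshold tables are commonly left to a statistical analysis plan, which is not shown. That lowers the weight of the point. It does not remove it, because the protocol itself fixes which results become events and what is reported to the agency. A later laboratory table would supplement that event list but not correct it.

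A third reply is that dose change and treatment may substitute for each other, so that counts could match. This also stands (step 4): the text makes an excess on eplerenone likely but does not prove it.

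Finally, exempting laboratory abnormalities that prompt no action is a coherent and stated rule. That is so. The difficulty here is its use for the trial's two named safety parameters when one arm lacks one of the qualifying actions.

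The event window is a separate matter: "Events and side effects will be registered from the time of initial dosing of study medication until withdrawal" names a start that controls do not have. Correcting it would leave the present asymmetry in place.

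**Conclusion.** The point holds in limited form. Followed as written, the rule ascertains laboratory events differently in the two arms and leaves tolerated high values out of the event list. That follows from the text alone.

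The likely direction is a relative excess on eplerenone, which would overstate rather than hide harm. It assumes that treatment is started about equally often in both arms for the same value. The range of 1.20 to 8.20 illustrates t between 0.1 and 0.5 and d between 0.2 and 0.8. It is not an estimate, and a reader should not take any particular inflation from it.

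The consequence is confined to event counts. It is greatest for potassium, which has no planned comparison. It is smaller for creatinine, which is compared as a mean, although a t test of means does not show how many patients had a marked rise.

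**What to change.** Add to the section on adverse events that, for p-potassium and p-creatinine, the number of patients in each arm exceeding prespecified values will be tabulated from the laboratory database. The table is given in the final report alongside the events, whatever action followed, and any action taken is recorded separately. The values must be identical in both arms and used only for reporting.

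Two figures already in the protocol can serve as example cut-points: the 5.0 mM potassium limit in 3.8 and the 30% creatinine rise over baseline in 3.9. Neither was written for this purpose. The first is an entry limit, and a patient may enter at exactly 5.0 mM. The second is a withdrawal criterion that requires the rise to persist and ties it to the first control visit. The table should therefore label both as reporting cut-points only.

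With up to 80 × 7 = 560 post-baseline potassium values, a higher potassium cut-point should be shown beside 5.0 mM so that trivial excesses do not dominate. No dose, treatment or withdrawal rule changes.

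The cost is protocol wording, a separate record of any action taken, and a slightly longer safety table. No new measurements are needed.

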### 3.13 Practical performance of study

Patients who fulfil the inclusion criteria and who are interested in participating in the study are informed about the study. The written information is handed out and will be thoroughly explained. A form of written informed consent is to be signed by the patient and the informant/investigator. If consent is given, dates for the study days will be given.

Demographic data will be registered.

Randomization: When inclusion criteria are met including the performance of a screening for PW measurements and the run-in period has been completed, patients are randomized to the active treatment arm with eplerenone or the control arm for 24 weeks.

Planning:

A deviation of ± 1 week from the initially planned date for visits is permitted. Collection of 24 hour urine is allowed for at time deviation of ± 3 days with respect to blood sampling. Participants’ visits are planned to be identical in both groups.

Visits are planned as shown below:

| ***Visit number*** | ***Time with reference to inclusion for the individual patient*** | ***Purpose of visit*** | ***Estimated time used for the visit*** |
| --- | --- | --- | --- |
|  | Screening | signing of written informed consent, PW measurement test, ECG, blood sampling, demographic data noted | 1-1½ hours |
| 1a | Week 1 | randomization, PW measurement, AMBP, blood sampling, 24 h urine, study medication handed out | 1 hour |
| 1b | Week 1 | return of AMBP device | 10 minutes |
| 2 | Week 2 | blood sampling, BP, increase in study medication | 30 minutes |
| 3 | Week 4 | blood sampling, BP, study medication handed out | 30 minutes |
| 4 | Week 8 | blood sampling, BP, study medication handed out | 30 minutes |
| 5a | Week 12 | PW measurement, AMBP, blood sampling, 24 h urine, study medication handed out | 1 hour |
| 5b | Week 12 | return of AMBP device | 10 minutes |
| 6 | Week 16 | blood sampling, BP, study medication handed out | 30 minutes |
| 7 | Week 20 | blood sampling, BP, study medication handed out | 30 minutes |
| 8a | Week 24 | PW measurement, AMBP, blood sampling, 24 h urine, study medication and packages returned | 1-1½ hours |
| 8b | Week 24 | return of AMBP device | 10 minutes |

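### Clinical adverse events have no registration period in the control arm, because registration starts at the first dose of a drug that controls never receive

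*Protocol*

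**What the plan says.** The protocol section on adverse events and side effects gives a single registration period: "Events and side effects will be registered from the time of initial dosing of study medication until withdrawal". The same section sends events to the CRF but leaves out laboratory values beyond the reference range "but where no action is taken to either change the study medication or institute treatment". It also promises a listing of events and side effects in the final report to the medicines agency.

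Section 3.4 defines the drug: "The study medication is eplerenone, a selective aldosterone receptor antagonist". For the comparator it says: "The control group will continue their usual medical therapy". No placebo is described. Section 3.13 states that "patients are randomized to the active treatment arm with eplerenone or the control arm for 24 weeks".

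The schedule does not differ by arm. Section 3.2 says "The study plan is identical for the two groups", and section 3.13 says "Participants’ visits are planned to be identical in both groups". Section 3.3 adds that "P-potassium and p-creatinine are used for safety monitoring".

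**The concern.** The registration period is anchored to something that happens in only one arm. A control patient has no initial dose, so a site that follows the text has no date from which to start recording that patient's events. The sentence covers events as well as side effects, so it cannot be set aside as a rule about drug reactions alone.

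What is at stake is the comparison of clinical events. The section on ethical considerations lists nausea, diarrhoea, dizziness and hypotension as common side effects, and atrial fibrillation and myocardial infarction as uncommon ones. Such events can plausibly occur without eplerenone in patients with CKD stages 3-4. Without control counts over the same period, the trial cannot say how many of the events seen on eplerenone exceed the background rate. This is a data-collection rule, so a statistical analysis plan cannot repair it afterwards.

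**Working it through.** The protocol gives no calculated figure on this point, so the check sets its rules side by side, arm by arm. The inputs are the registration and laboratory rules (adverse events section), the definitions of study medication and control (3.4), the laboratory and visit tables (3.11 and 3.13), the withdrawal criteria (3.9) and the planned size (Statistics: 40 per group).

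| Item, as written | Eplerenone arm (40 planned) | Control arm (40 planned) |
| --- | --- | --- |
| Start of event registration | First dose; drug is handed out at visit 1a | None stated |
| End of registration, patient withdrawn | Withdrawal | Withdrawal, but no period has begun |
| End of registration, patient completes 24 weeks | None stated | None stated |
| Laboratory trigger 1: study medication changed | Can occur | Cannot occur |
| Laboratory trigger 2: treatment started | Can occur | Can occur |
| Potassium and creatinine | Screening and visits 1a, 2, 3, 4, 5a, 6, 7, 8a | Same |
| Blood pressure (office or ambulatory) | Visits 1a, 2, 3, 4, 5a, 6, 7, 8a | Same |

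**Share affected.** 40 / (40 + 40) = 50% of planned patients have no defined start of event registration. No other section supplies one.

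**Laboratory rule.** Suppose the same out-of-range potassium value arises in both arms. If it is met on eplerenone by a change of study medication, it is recorded. If the control patient is given no treatment for it, it is not recorded. If both patients are treated, both values qualify. The asymmetry concerns one of two triggers and affects the event listing, not the measured values.

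**End of the period.** Section 3.9 uses withdrawal to mean leaving the study. A patient who attends visit 8a has not withdrawn, so the text gives that patient no closing date.

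**What cannot be estimated.** Let *e* be the event proportion on eplerenone and *c* the proportion in controls. The quantity of interest is *e* - *c*. Under the written rule only *e* is observed, so the difference is unknown by the whole of *c*. The protocol gives no value for *c*.

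**Scale of the counts.** The protocol places common side effects of the drug between 1% and 10%. At those limits the 40 eplerenone patients would yield 40 × 0.01 = 0.4 to 40 × 0.10 = 4 patients with a given effect. The chance of seeing at least one is 1 - 0.99^40 = 0.33 to 1 - 0.90^40 = 0.99. Even with full recording in both arms, the comparison would be descriptive.

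**The case against.** The best defence is that the phrase is loose drafting. The protocol writes shared procedures in the language of the active arm: its visit table hands out study medication at visits said to be the same in both groups. Randomisation and first hand-out share visit 1a, so the first dose may simply mark the start of the study period. The sentence on recording events in the CRF names no arm, section 3.10 provides a CRF for every patient, and nothing expressly excludes controls. This shows that sites might record control events. It does not give them a rule to do so, and no other start point appears, so the gap stands.

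Several stronger inferences do fail:

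- A reader might conclude that the control arm yields no safety data at all. It does yield some: potassium, creatinine and blood pressure follow one schedule in both arms, and the withdrawal criteria apply to every participant. Laboratory hyperkalaemia and renal function, risks the protocol stresses, can be compared.
- A reader might take the laboratory rule to exclude controls. It does not, because starting treatment is a trigger in either arm.
- A reader might say that the plan attributes every registered event to eplerenone. The text makes no such attribution; it speaks of events, side effects and suspected reactions separately.
- A reader might put a number on the overstated risk by assuming a control rate. The answer would only return the assumed rate, and the 1-10% band describes the drug's side effects, not a control rate.
- A reader might think that events are lost once the drug is stopped, or that the event causing withdrawal is missed. Registration ends at withdrawal from the study, not at stopping the drug, and the event that prompts withdrawal falls before that point.

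**Conclusion.** The point holds in a limited form. As written, clinical (non-laboratory) adverse events have no registration period for the 40 planned control patients, half of the trial, so their rates cannot be compared between arms. In addition, completers have no stated end of registration, and one of the two laboratory recording triggers cannot operate in controls. Scheduled potassium, creatinine and blood pressure data remain comparable.

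This rests on reading the registration sentence literally and on the absence of any other start point in the protocol. How sites would act in practice is not known. The primary PWV comparison, its power and the randomisation are untouched, so this is not a must-fix for the primary conclusion. It is worth correcting before enrolment, because unrecorded events cannot be recovered.

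**What to change.** Replace the registration sentence with one that applies to both arms: events and side effects are registered from randomisation (visit 1a) to the week-24 visit, or to withdrawal from the study if that comes first, whether or not study medication has been stopped. Word the laboratory recording rule so that the same result is handled in the same way in both arms, without reference to study medication. State that events, p-potassium and p-creatinine will be tabulated by arm.

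The cost is small: a reworded passage, and extra CRF recording for control patients at visits already scheduled. Patients who withdraw return to routine outpatient care under section 3.9, so following them to week 24 would need contacts that the protocol does not plan. The wording above therefore closes their period at withdrawal.
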